## **Study Protocol**

### **Study Title: Skills for Change: Development, Implementation and Evaluation of a Community-based Diabetes Nutrition Education Program for Emirati Adults with Type 2 Diabetes**

#### **Project Summary:**

##### **Project Summary:**

The United Arab Emirates (UAE) with a prevalence of 19.5% of diabetes is considered by the International Diabetes Federation as the country with the second highest prevalence of diabetes in the world. Diabetes is a major risk factor for coronary artery disease, a leading cause of death in the United Arab Emirates. Other complications associated with type 2 diabetes are neuropathy and microvascular damage leading to blindness, and end-stage renal disease. Effective diabetes self-management requires that persons with diabetes acquire the necessary knowledge and skills to change their nutrition-related behaviors for optimal metabolic control. Evidence from randomized controlled studies, observational studies, and meta-analyses support the effectiveness of medical nutrition therapy for diabetes management. Despite the high prevalence of diabetes and its complications in the UAE, very few diabetes education intervention studies have been conducted in representative populations in the country.

We propose a one-year, community-based, cluster randomized study involving 400 Emirati adults with type 2 diabetes that will focus on diet and physical activity to decrease sedentary lifestyle and improve food choices and clinical outcomes, including glycemic control and blood lipids. The primary outcome of the intervention is a change in HbA1c. We expect this project driven by theoretical principles of behavior change and education will enhance the diabetes-related knowledge, skills, and behaviors of the participants. The results of this project will serve as an important guide in the development and implementation of culturally adapted future diabetes management nutrition intervention programs for Emirati adults with type 2 diabetes. The study will be conducted in collaboration with Al Ain Ambulatory Healthcare Services, Abu Dhabi Healthcare Services.

#### **Rationale & Background Information**

Diabetes mellitus and its complications are major causes of morbidity and mortality and contribute substantially to healthcare costs. The United Nations General Assembly passed a resolution in 2007 recognizing November 14th as World Diabetes Day and it encouraged all member states to develop national strategies and policies for the prevention, treatment, and care of people with diabetes. According to the International Diabetes Federation, the United Arab

Emirates (UAE) has the second highest prevalence of diabetes (19.5%) in the world (IDF, 2007). The prevalence of diabetes for only the Emirati adult population is nearly 25% (Malik, et al, 2005). Persons with diabetes have a 2 to 4-fold greater risk of cardiovascular disease than those without diabetes (Roglic et al 2005). According to the Ministry of Health coronary artery disease is a leading cause of death in the United Arab Emirates (Department of Preventive Medicine, 2006) and diabetes-related heart problems were the biggest killer in the UAE in 2008, accounting for 31.6 per cent of deaths. Diabetes is also a major economic burden to the country (\$100-\$200 million annually) (GulfNews, Sept 14, 2009). A study involving a random sample of UAE citizens living in Al Ain found that only 33.3% of subjects with diagnosed diabetes achieved metabolic control (HbA1c <7%) to reduce their risk of diabetes related complications (Saadi, et al, 2007).

A recent review highlighted the high prevalence of overweight, obesity, and diet-related non-communicable diseases in the UAE population (Ng et al, 2010). Results from a community-based survey on risk factors for cardiovascular disease conducted among 817 national residents of Al Ain city found that high waist circumference was significantly associated with hypertension and high BMI with diabetes (Baynouna et al, 2009). A previous chronic disease management intervention in the Al Ain Ambulatory Healthcare Services health centers showed improvements in glycemic control, blood lipid profiles, and blood pressure. However, lifestyle-related factors of cardiovascular disease, such as diet and physical activity did not improve possibly due to the limited access to dietitians and other health education specialists to reinforce the physician messages (Baynouna et al, 2010). Saadi and colleagues (2007) found that among people diagnosed with diabetes, only 44% reported seeing a dietitian and 26% of them reported that they did not follow any diet to manage their diabetes.

Evidence from randomized controlled studies, observational studies, and meta-analysis supports the effectiveness of medical nutrition therapy for diabetes (Pastors et al, 2002; Pastors et al, 2003). Diabetes self-management interventions, including those related to weight management, and physical activity have been shown to improve patterns of diabetes management and metabolic control among adults with type 2 diabetes (Norris et al, 2002). Besides, metabolic control achieved through medical nutrition therapy, physical activity, and medications (when needed) improves the quality of life and treats and prevents diabetes complications (ADA, 2007). The UK Prospective Diabetes Study showed that for every percentage decrease in glycosylated hemoglobin (HbA1c), there was a 37% reduction in the risk for microvascular complications and a 21% reduction in the risk for any - **endpoint** or death related to diabetes (Stratton, 2000). Studies on diabetes medical nutrition therapy (MNT) reported reductions in HbA1c, ranging from 0.25% to 2.9%, depending on the type and duration of diabetes. Individual sessions of MNT in these studies ranged from 1 to 5 hours or were a series of 10 to 12 group sessions (2 hours each) (ADA Evidence Analysis Library, 2010).

Although diets high in fresh fruits, vegetables, and whole grains and lower in saturated fat have protective effects from cardiovascular disease, the leading cause of mortality for people with diabetes, many people with diabetes may not be getting the daily recommended number of fruits, vegetables, and whole grains. However, studies conducted with other populations without type 2 diabetes reported strong correlates between nutrition knowledge, attitudes, perceived beliefs, barriers, and intake of fruits and vegetables among adults (Steptoe et al, 2004; Watters et al, 2007).

Physical activity plays a major role in the prevention and control of insulin resistance, pre-diabetes, and type 2 diabetes (Coldberg, 2007). One prospective cohort showed that walking at least 2 hours per week was associated with a reduction in the incidence of premature death by 39% - 54% from any cause and 34% - 53% from cardiovascular disease among patients with diabetes (Gregg et al, 2003). The American Diabetes Association (ADA) recommends that adults with type 2 diabetes accumulate at least 150 minutes of moderate-intensity aerobic exercise and 3 sessions of resistance exercise per week (Sigal et al., 2006).

The Cochrane Database of Systematic Reviews has evaluated the effectiveness of culturally appropriate diabetes health education as an important outcome measure in type 2 diabetes and has concluded that culturally appropriate diabetes health education at least for the short term has a positive impact on glycemic control, knowledge of diabetes, and healthy lifestyles (Hawthorne et al, 2008). Furthermore, self-management education improves glycemic control at immediate follow-up, and increased contact time increases the effect (Norris et al, 2002). However, Further research is needed to assess the effectiveness of self-management interventions on sustained glycemic control, cardiovascular disease risk factors, and ultimately, microvascular and cardiovascular disease and quality of life (Norris et al, 2001).

To increase the likelihood of changing lifestyle behaviors, interventions, such as diabetes education programs often incorporate behavior change theories (Vallis et al, 2003; Parchman et al, 2003), including the Transtheoretical Model (Prochaska & DiClemente, 1982) and the Social Cognitive Theory (Bandura, 1986). The Transtheoretical Model of Behavior Change (TTM) (Prochaska & DiClemente, 1982) provides a framework for predicting a client's willingness to change lifestyle behaviors and is useful in facilitating persons with diabetes to modify and maintain new behaviors. The Social Cognitive Theory (SCT) is helpful in understanding and predicting both individual and group behavior and identifying methods by which behavior can be modified or changed (Bandura, 2001). It provides a framework for designing, implementing, and evaluating programs and is useful in predicting diabetes self-management behaviors, such as diet, self-monitoring of blood glucose, and physical activity (Glasgow, et al, 2002; Hays & Clark, 1999).

Despite the high prevalence of diabetes and its complications in the UAE, many people with diabetes do not receive advice on diabetes management from dietitians (Afandi, et al. 2006). A recent study found that although the majority of the persons with diabetes attending health centers have uncontrolled diabetes and excess body weight, less than half of them (46%) had ever received nutrition counseling from a dietitian (Al-Kaabi, et al, 2008). Additionally, there is limited research on nutrition knowledge related to diabetes management of persons with diabetes in the United Arab Emirates. A recent study involving a convenient sample of Emirati and Omani adults with diabetes reported low nutrition knowledge related to carbohydrate-containing foods (Ali et al, 2008). However, the main limitation of this study was that it involved a relatively small sample of volunteers. Similarly, in the UAE, although a worrying lack of physical activity was pointed out (Mabry et al, 2010), large community interventions including physical activity to improve the management of type 2 diabetes are still missing leading to a huge gap in terms of adapted approach, education and actions in the field of physical activity in this local population.

Therefore, further studies involving larger, more representative samples of Emirati adults with diabetes are needed to gain a greater understanding of diet and diabetes self-management

behaviors of individuals with diabetes in the UAE. We propose a collaborative project driven by theoretical models of behavior change and adult education principles with Al Ain Ambulatory Healthcare Services to evaluate the feasibility and effectiveness of a culturally appropriate, community-based diabetes nutrition education program for Emirati adults with type 2 diabetes. The project aims to improve nutrition knowledge, promote healthy diets (increased fruit and vegetable intake, reduced intake of saturated fat), and increase physical activity among Emirati adults with type 2 diabetes. The impact of the intervention procedures on metabolic control, anthropometric measurements, and cardiovascular risk lipid profiles will be investigated.

### **Study Aims and objectives**

The overall aim of this research project is to design and implement a community-based diabetes nutrition education program to improve diet and physical activity behaviors as well as diabetes-related clinical outcomes among Emirati adults with type 2 diabetes attending Ambulatory Healthcare Services clinics in Al Ain City. The specific objectives are to:

1. Conduct a one-year intervention to evaluate the impact of an educational program on energy and nutrient intakes, nutrition knowledge, physical activity, and diabetes treatment satisfaction among Emirati adults with type 2 diabetes
2. Evaluate the impact of an educational program on diabetes-related clinical outcomes, including glycemic control, anthropometric measurements, and blood lipid profiles in Emirati adults with type 2 diabetes

### **Relevance of the proposed work to the UAE community:**

To our knowledge, this project is the first community-based intervention focusing mainly on diabetes nutrition education in the UAE and thus it can serve as an important guide in the development and implementation of future diabetes management intervention programs in the country. The potential Benefits of the intervention include (1) Improved nutrition knowledge and skills for diabetes care; (2) Healthier food choices and increased physical activity levels; (3) Improved clinical outcomes (blood glucose, body weight, and blood lipids); (4) Culturally-appropriate exercise video to increase the physical activity levels of adults with diabetes and families; (5) Model community-based diabetes nutrition intervention program that has the potential to improve participant nutrition knowledge and skills; (6) Appropriate recommendations for larger scale programs in the UAE that have the potential to improve nutrition knowledge, skills, and clinical outcomes of adults with diabetes; (7) Increased scientific knowledge: Identification of the potential impacts of culturally-adapted diet intervention and regular practice of moderate physical activity on metabolic parameters.

## **Methodology**

### **Design and Participants:**

The seven health centers managed by Al Ain Ambulatory Healthcare Services will be the target setting for this study. The primary end-point for this intervention is HbA1c. We aim at a difference in one-year HbA1c value of one-third of the standard deviation which is approximately 1.8 based on recent data from patients with diabetes attending Ambulatory Health Services clinics in the Emirate of Abu Dhabi. Thus, we expect a 0.6 decrease in HbA1c in the

intervention group. We chose to test this difference with a power of 0.8 and a 2-tailed significance level of 0.05. If randomization had been carried out on an individual basis, we would need  $16 \times 9 = 144$  participants per group. However, we have to take into account group randomization. Assuming a design effect of 2, we need approximately 300 per group. However, there will be a gain in efficiency by adjusting for baseline values. Therefore, 200 participants should be adequate per group (i.e. 200 for intervention and 200 for control). Based on this calculation, the seven health centers were randomly assigned as follows: 3 intervention clinics (Al Yahar, Al Muweiji, & Hilli) and 4 control clinics (Al Maqam, Al Zakher, Niyadat, & Mezyad). The health center setting (urban vs. suburban) and size (large vs. small) were considered during the randomization. The assignment of the health centers to the intervention versus control groups was stratified by the center sizes and center locations. Of the 7 health centers, 3 are large urban centers, two are small urban centers, and two are large suburban centers. One large urban, one large suburban and two small urban centers were randomly assigned to the control group, and the remaining 3 centers were assigned to the intervention group.

Exclusion criteria are: Very advanced age (>70 Y), patients with severe complications, such as renal or heart failure, blindness, or other morbidities that can prevent active participation in the program. Moreover, patients with contraindications to the required physical activity may be excluded from the structured physical activity program upon the recommendation of their attending physicians. Verbal and written informed consent will be obtained from all the participants. Ethics approval for the project will be obtained from the relevant research ethics committees (UAE University Research Affairs and Al Ain Medical District Human Research Ethics Committee).

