### **Problems Anticipated**

Potential challenges of the study implementation include recruitment and retention challenges of participants as well as adherence to the educational component of the study. Moreover, given this study will be the first nutrition intervention program for Emirati adults with type 2 diabetes, additional challenges may occur. Active involvement of the healthcare professionals working in these health centers in the study implementation as well as keeping frequent contact with the participants will be used to minimize these challenges.

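### The stated power of 0.8 with 200 participants per group is not supported: normal critical values with seven centres, a cut for baseline adjustment with no stated correlation, and no allowance for loss

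*Protocol*

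**What the plan says.** The calculation is in the protocol, Methodology, Design and Participants. It runs in five steps.

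- Effect: "We aim at a difference in one-year HbA1c value of one-third of the standard deviation which is approximately 1.8", that is, 0.6 HbA1c points.
- Error rates: "We chose to test this difference with a power of 0.8 and a 2-tailed significance level of 0.05".
- Individual randomisation: 16 × 9 = 144 per group.
- Clustering: "Assuming a design effect of 2, we need approximately 300 per group". No ICC or centre size is given.
- Baseline adjustment: "However, there will be a gain in efficiency by adjusting for baseline values". No correlation is given. The conclusion follows directly: "Therefore, 200 participants should be adequate per group (i.e. 200 for intervention and 200 for control").

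The same section reports seven randomised health centres, three intervention and four control, stratified by size and location. The Data analysis section says that the 12-month comparison will take account of the multilevel structure, without naming a model. The section on anticipated problems says: "Potential challenges of the study implementation include recruitment and retention challenges of participants". The calculation contains no allowance for loss.

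**The concern.** The factor 16 in the 144 comes from normal critical values (1.96 and 0.84). A test that respects the randomisation of seven centres has at most about 7 − 2 = 5 degrees of freedom between centres, with a two-sided 5% critical value of 2.571. A design effect inflates the variance; it does not change the critical value. The power shown is therefore not that of the clustered comparison the protocol commits to.

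The step from about 300 to 200 removes a third of the sample on a gain that is asserted but not quantified, so a reader cannot reproduce 200 from the stated inputs. All 400 participants are counted as analysed at 12 months.

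HbA1c is the primary endpoint, and the results are meant to guide later programmes. If the trial finds no difference, readers will take the power of 0.8 as evidence that a 0.6-point effect was unlikely to be missed.

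**Working it through.** **Inputs from the protocol.** Difference 0.6, SD 1.8 (so d = 1/3), two-sided alpha 0.05, design effect (DE) 2, 200 analysed per group, centres 3 + 4. **Assumptions, because the protocol gives none:** the baseline to 12-month correlation r, the ICC and the loss rate. Baseline adjustment is taken to multiply the whole variance by 1 − r².

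**1. Reproducing the protocol's chain.**
- Individual n = 2(1.960 + 0.842)² / d² = 15.70 × 9 = 141.3, so 142 per group. The 16/d² rule gives 144, which agrees.
- 144 × 2 = 288, rounded up to about 300.
- The cut to 200 needs 1 − r² = 200/288 = 0.694 (r = 0.55) or 200/300 = 0.667 (r = 0.58). Neither value is stated.

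**2. Power at 200 per group, DE held at 2, no loss.** The standard error is SE = √[1.8² (1 − r²) × 2 × 2/200], and the noncentrality is 0.6/SE.
- r = 0.55: SE = √(3.24 × 0.694 × 0.02) = 0.212; noncentrality 2.83.
- r = 0.58: SE = √(3.24 × 0.667 × 0.02) = 0.208; noncentrality 2.89.

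| | Normal (1.960) | t on 5 df (2.571) |
|---|---|---|
| r = 0.55 | 0.81 | 0.62 |
| r = 0.58 | 0.82 | 0.64 |
| 300 per group, no adjustment | 0.82 | 0.64 |

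The last row has SE² = 3.24 × 2 × 2/300 = 0.0432, the same as r = 0.58 at 200. The shortfall is therefore already present before the cut.

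**3. Milder reading: ICC fixed, DE shrinks at 200 per group.** If DE 2 belongs to 288 to 300 per group, then ICC = 1/(m − 1), where m is the centre size. With 288 in three centres, m = 96 and ICC = 0.0105. With 300 in four centres, m = 75 and ICC = 0.0135. At 200 per group the centres hold 66.7 (intervention) or 50 (control).
- ICC 0.0105: DE = 1 + 65.7 × 0.0105 = 1.69 and 1 + 49 × 0.0105 = 1.52, sum 3.21. At r = 0.58, SE = √(2.16 × 3.21/200) = 0.186, noncentrality 3.22, power on 5 df 0.73.
- ICC 0.0135: DE = 1.89 and 1.66, sum 3.55. At r = 0.55, SE = √(2.25 × 3.55/200) = 0.200, noncentrality 3.00, power on 5 df 0.67.

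**4. Loss (assumed rates), at r = 0.55 to 0.58, on 5 df.**
- DE held at 2: 0.58 to 0.60 with 10% loss; 0.53 to 0.55 with 20%.
- ICC fixed at 0.018 (DE 2 at 400/7 = 57 per centre): 0.57 to 0.59 with 20% loss.
- ICC fixed at 0.012 (DE 2 at 600/7 = 86 per centre, within the milder range): 0.64 to 0.66 with 20% loss.

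**5. What would give 0.80.** On 5 df the noncentrality must be 3.514, so SE = 0.6/3.514 = 0.1707 and SE² = 0.0292.
- DE 2: 1 − r² = 0.0292 × 200/(3.24 × 4) = 0.450, so r = 0.74.
- Milder reading: with 3.21 or 3.55 in place of 4, r = 0.66 or 0.70.
- With loss and DE 2: r = 0.77 at 10% and 0.80 at 20%.

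**6. Detectable difference at 80% power, 5 df, no loss.** This is 3.514 × SE: 0.73 to 0.75 points at DE 2, and 0.65 to 0.70 on the milder reading.

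**The case against.** The strongest reply is that the shortfall depends on a correlation the protocol never gives. The back-solved 0.55 to 0.58 is the value that makes 200 come out of 288 or 300 under the protocol's own method; it is not a stated assumption. At DE 2 with no loss, power on 5 df is 0.70 at r = 0.65, 0.75 at r = 0.70, and 0.88 at r = 0.80. A reader might infer that the trial is certainly underpowered for 0.6 points. The document does not support that, because a high enough correlation would deliver 0.80. This part of the reply stands, and it limits the point to power that is not supported.

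The milder reading of the design effect is also fair. It is applied at the step from 144 to about 300, and with seven fixed centres it would fall at 200 per group. Both readings are therefore shown. A reader might be tempted to try a much larger ICC, such as 0.05. That implies design effects of 1 + 65.7 × 0.05 = 4.3 and 1 + 49 × 0.05 = 3.5, against the stated 2, so it has no footing in the protocol.

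Finally, the model and the df method may properly sit in a statistical analysis plan, so 5 df is an assumption. It is a generous one: fitting the three strata would leave about 3 df, where power at DE 2 is 0.49 to 0.50, and both small urban centres are in the control arm. Using 1.96 with seven centres would raise the type I error rate, so it does not rescue the figure. The calculation itself, with its unstated inputs, is in the protocol and is open to comment there.

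**Conclusion.** The point holds as wrong as written. Each stated multiplication is right to rounding, but the conclusion of power 0.8 at 200 per group does not follow from the stated inputs, and at the correlation the cut implies it is not reached. For 0.6 points with no loss, power is about 0.62 to 0.64 with the design effect at 2, and about 0.67 to 0.73 on the milder reading. The chance of missing the effect is then roughly 27% to 38%, against the 20% claimed.

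With an assumed 20% loss, power falls to about 0.53 to 0.59 where the design effect is 2 at the planned 200 per group, and to about 0.64 to 0.66 at an ICC of 0.012. These figures rest on 5 df, on r of 0.55 to 0.58 and on the ICC values derived from the design effect of 2. None of these is stated in the protocol.

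A reader might also infer that the estimate, its confidence interval or the type I error is compromised. Nothing in the sample size paragraph shows that; what it affects is how a null result would be read.

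**What to change.** Keep the 400 participants and the seven centres, and rewrite the sample size paragraph as follows.

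- State the assumed ICC with the centre sizes it applies to, the assumed baseline to 12-month HbA1c correlation, and the expected loss, each with its source.
- Recompute power with the t-distribution on the between-centre degrees of freedom, consistent with the planned analysis and with any stratum terms.
- Replace the claim of power 0.8 with the resulting power for 0.6 points, or with the difference detectable at 80% power. At the implied correlation that difference is about 0.65 to 0.75 points without loss, and larger with loss.
- Show a range over the uncertain inputs. No single replacement figure can be prescribed from this document.

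The cost is one rewritten paragraph and probably a less favourable stated figure. No participants or centres are added.
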